### **6.3.2 Sample Size Calculation for WIdO / DGU Trauma Register**

In 2019, approximately 11,000 insured individuals aged 18-55 with a severe injury treated in an acute hospital were identified based on the existing identification criteria in the nationwide WIdO data. Over a three-year inclusion period, around 33,000 severely and critically injured insured individuals will be included in the study. With this target sample size, precise estimates of prevalences are also possible within small subgroups. For instance, in a subgroup of 5% of the total number of patients, a prevalence of 50% could be estimated with a precision of  $\pm 1.20\%$  to  $1.38\%$  (two-sided exact binomial confidence interval 95% confidence interval). A prevalence of 50% was chosen as it shows the greatest variation. Higher or lower prevalences, as well as larger subgroups, would lead to a more precise estimate.

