## **4. Scientific Background**

In Germany, approximately 30,000 people suffer a severe trauma each year (annual reports of the “Trauma Register DGU”). In recent decades, significant progress in preclinical and clinical treatment has markedly reduced the mortality rate of severely injured patients (Ruchholtz et al., 2008). With increasing survival rates, the functional outcomes and health-related quality of life of these patients are becoming more important. Affected patients suffer from chronic pain, psychosomatic disorders, and unemployment (Simmel et al., 2010; Simmel et al., 2013), as well as increased post-traumatic morbidity (Bouillon et al., 1998; Holtslag et al., 2007; von Rüden et al., 2013).

The return of patients to the workforce is important to promote their quality of life and social participation and to reduce the socioeconomic burden on society due to disability. According to current data from the “Trauma Register DGU,” 60% of severely injured patients in Germany are of working age (18-65 years), and three-quarters are male. With a current legal retirement age of 67 years, disability can lead to a financial gap of several decades. The high unemployment rate after trauma is well-known. According to the Hannover Polytrauma Long-Term Study (HLPS) (Sittaro et al., 2007), an average of about 22% of patients who were previously able to work are unemployed. Another 16% have undergone retraining due to their

accident to maintain work ability, and 24% have been classified for early retirement due to the accident. According to a Dutch study, only 58.5% of the severely injured patients of working age who were followed up were able to engage in full-time employment 15 months after the trauma, and an additional 21.5% could only pursue part-time employment (Holtslag et al., 2007). According to data from a pilot study on outcome assessment, only about 30% of all severely injured patients in Germany are able to work again two years after an accident (Kamp et al., 2019).

Following predictors of clinical treatment for disability have already been identified: patient age, severity of injury, traumatic brain injury, duration of intensive medical treatment, psychological sequelae, subjective perception of the injury, and the patient's education level (Frink et al., 2014; Kaske et al., 2014).

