| Study Part          | Inclusion Criteria                                                                                                                                                                                                                                                                                                                                                 | Exclusion Criteria                                                                                                                                                                                              |
|----------------------------|---------------------------------------------------------------------------------------------------------------------------------------------------------------------------------------------------------------------------------------------------------------------------------------------------------------------------------------------------------------------------|------------------------------------------------------------------------------------------------------------------------------------------------------------------------------------------------------------------------|
|                            | 
 
• All patients documented in the TR with a MAIS* <math>\geq 3</math>,
 
• Acute stay survived
 
• Age 18-55 years
 
• Accident date 2015-2017
 
                                                                                                                                                      | 
 
• Patients after a suicide attempt
 
• Patients who are not communicative after the acute phase (inclusion point) (Glasgow Outcome Score <math>< 8</math>)
 
 |
| WIdO Secondary Data | 
 
• Insured individuals of working age (18-55 years)
 
• Severe acute hospital-treated injury survived between 2015 and 2017 and continuously insured during the observation period. The defined severe injury must correspond to a MAIS* of at least 3 (MAIS <math>\geq 3</math>) or an ISS* <math>\geq 9</math>.
 
 |                                                                                                                                                                                                                        |

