#### WIdO:

Since the coding guidelines of ICD-10GM (= International Statistical Classification of Diseases and Related Health Problems, German Modification) do not allow for coding of MAIS or ISS, the existing identification criteria based on medical expertise will first be revised. These will be operationalizable in secondary data through combinations of specific ICD-10GM codes, OPS codes (= Operation and Procedure Key, version 2019), and DRGs. The first hospitalized injury that meets the inclusion criteria will be considered the index stay of the insured. The three-year follow-up period starts with the discharge from the index stay.

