**Tab. 4: Sample Size Planning**

| Study Part               | Sample Size (n=)                        |
|---------------------------------|------------------------------------------------|
| Prospective Cohort Study | 1000 severely and critically injured patients  |
| WIdO Data                | 33,000 severely and critically injured insured |
| DGU Trauma Register      | 29,345 (Base collective in 2019)               |

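### The planned sizes of the two retrospective arms do not describe those arms as defined: the register figure is an unfiltered 2019 count, and the WIdO figure states no allowance for survival or continuous insurance

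*Protocol*

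**What the plan says.** **WIdO arm.** Section 6.3.2 starts from one year: "In 2019, approximately 11,000 insured individuals aged 18-55 with a severe injury treated in an acute hospital were identified". It then projects: "Over a three-year inclusion period, around 33,000 severely and critically injured insured individuals will be included in the study". Tab. 4 repeats the total as "33,000 severely and critically injured insured". The same paragraph of 6.3.2 bases a precision statement on this size: in a subgroup of 5% of patients, a 50% prevalence would be estimated to within ±1.20% to 1.38%, with a two-sided exact 95% interval.

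The eligibility rule in Tab. 3 asks for more than an age band and a hospital-treated injury: "Severe acute hospital-treated injury survived between 2015 and 2017 and continuously insured during the observation period". The WIdO paragraph of 6.1.1 adds three things: the existing identification criteria are to be revised before use, follow-up lasts three years from discharge, and each person enters once ("The first hospitalized injury that meets the inclusion criteria will be considered the index stay of the insured"). Section 7.1.3 limits the data to 2015-2020.

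**Register arm.** Tab. 4 gives the size as "29,345 (Base collective in 2019". Tab. 3 restricts this arm to patients with MAIS of at least 3 who survived the acute stay, were aged 18-55 and had their accident in 2015-2017. It excludes suicide attempts and patients who cannot communicate. Section 7.1.4 confirms the years 2015 to 2017.

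**The concern.** A planned size should be the number of people that the eligibility rules deliver. Neither figure is shown to be that.

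For the register, the mismatch is visible from the label alone. The figure belongs to 2019, and the arm admits only accidents from 2015-2017, so nobody counted in it for a 2019 accident is eligible. It also covers one year rather than three, and applies neither the age nor the survival restriction.

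For WIdO, a 2019 count is carried over to 2015-2017, and two eligibility rules that can only remove people do not appear in the calculation. The identification algorithm behind the count is also not yet final. Section 6.3.2 attaches its precision claim to this size, so the size and the claimed precision stand or fall together.

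**Working it through.** **Inputs from the protocol**
- WIdO: about 11,000 in 2019, aged 18-55; three inclusion years; 5% subgroup; 50% prevalence; exact two-sided 95% interval (6.3.2).
- WIdO follow-up of three years from discharge (6.1.1); data from 2015 to 2020 (7.1.3).
- Register: 29,345, base collective 2019 (Tab. 4).
- Deaths of about 10%, stated for Level-1 centres in the prospective cohort (6.3.1) and borrowed here.
- Age share (section 4): "60% of severely injured patients in Germany are of working age (18-65 years". Ages 18-55 lie within that band, so 60% is an upper limit for them.

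**Assumptions, not in the protocol**
- WIdO survival 90-100%, with the lower end borrowed from 6.3.1.
- Continuous insurance over three years 80-100%.
- Register share aged 18-55 between 40% and 60%.
- Each register year as large as 2019.

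**1. Reproduce the WIdO size.** 11,000 × 3 = 33,000. The multiplication is correct.

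**2. Could the insurance rule already be in the 11,000?** Read the observation period as the three-year follow-up. A person injured at the start of 2019 has at most two years of observation by the end of 2020. Three years of continuous insurance therefore cannot have been required of the 2019 cases in these data. For survival there is no such proof: 6.3.2 does not say whether deaths were removed.

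**3. Check the stated precision at the stated size.** 5% × 33,000 = 1,650. The exact 95% half-width at 50% is 2.44 points. The normal approximation gives 1.96 × √(0.25/1,650) = 2.41 points. Inverting, n = 0.25 × (1.96/h)²:
- h = 1.20% needs about 6,670 patients, or 20% of 33,000.
- h = 1.38% needs about 5,040 patients, or 15% of 33,000.

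The stated precision therefore belongs to subgroups of about 15-20%, not 5%.

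**4. Effect of the two unstated filters on WIdO.** Size = 33,000 × survival × insured share.

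| Survival | Insured | Cohort | 5% subgroup | Exact half-width (points) |
|---|---|---|---|---|
| 100% | 100% | 33,000 | 1,650 | 2.44 |
| 90% | 100% | 29,700 | 1,485 | 2.57 |
| 90% | 90% | 26,730 | 1,336 | 2.72 |
| 90% | 80% | 23,760 | 1,188 | 2.88 |

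**5. Register.**
- Age alone, one year: 29,345 × 0.60 = 17,607 at most.
- With 10% deaths: 29,345 × 0.60 × 0.90 = 15,846 per year, and × 3 = about 47,500.
- With a 40% age share: 29,345 × 0.40 × 0.90 = 10,564 per year, and × 3 = about 31,700.
- The three-year count equals 29,345 when the share aged 18-55 is 1/(3 × 0.90) = 37%. Below that share it is smaller, above it larger. The remaining exclusions would lower every count by an amount the protocol does not give.

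**The case against.** Much can be said for the plan. Its arithmetic is right, and the figures are offered as approximate. Neither arm recruits; both use whatever records qualify, so a wrong forecast does not stop the work. No precision figure depends on the register number, which Tab. 4 labels openly as 2019, and that arm serves description and representativeness. For WIdO, going from 33,000 to about 23,800 moves the half-width only from 2.44 to 2.88 points. All of this stands and keeps the point moderate. It does not make 29,345 a count of the arm, and it does not supply the missing insurance allowance.

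A reader might infer several stronger things that the protocol does not support:
- **That the WIdO count ignores age.** It does not. The 11,000 are already aged 18-55, and they are counted as individuals. Age is missing only from the register figure, and continuous insurance is a rule only for WIdO.
- **That 33,000 is certain not to be reached.** The 10% mortality is borrowed from Level-1 centres, the insurance share is assumed, and yearly counts in 2015-2017 may differ from 2019.
- **That 11,000 is implausible for one insurer.** Section 4 gives about 30,000 severe traumas a year, and 60% of that is 18,000. But that figure comes from register reports, and the register takes emergency-room admissions with subsequent intensive therapy. WIdO uses code combinations for MAIS of at least 3 or ISS of at least 9. The definitions differ, so the ratio proves nothing.
- **That the revised codes will shrink the cohort sharply.** The protocol says only that the criteria will be revised, not in which direction.
- **That both sizes must fall.** The register count for three years may well exceed 29,345.

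**Conclusion.** The point holds in limited form.

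**Register:** 29,345 describes the wrong population: one year outside the eligible period, without the age and survival filters. Under the protocol's own 60% it is not a one-year count for this arm. Whether the eligible three-year count is above or below it cannot be settled from the protocol.

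**WIdO:** 33,000 is a projection from 2019 under criteria that will change, with no stated allowance for survival or insurance. The insurance rule cannot have been applied in full to the input, provided that the observation period means the three-year follow-up and the count came from the data window in 7.1.3. Under the assumed ranges the cohort is about 23,800 to 33,000, with a 5% subgroup half-width of about 2.9 to 2.4 points.

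The larger numerical error is the stated precision, which is too optimistic by a factor of about 1.8 to 2.0 (2.44/1.38 and 2.44/1.20) even at 33,000. That result needs no assumption about attrition. None of this undermines the choice of data sources or the analyses. It should be corrected because readers will take these figures as the size and precision of the two arms.

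**What to change.** 1. Have WIdO run the revised identification algorithm with every Tab. 3 filter and the first-stay rule on 2015-2017, and put that count in 6.3.2 and Tab. 4 in place of 33,000. Until it is available, give a range and label it as resting on assumed survival and insurance shares.
2. Restate the 5% subgroup precision from that count. If 33,000 is kept for the time being, the figure is ±2.44 points; alternatively, name the subgroup share that the stated precision belongs to.
3. Replace 29,345 by the register count for 2015-2017 under the Tab. 3 criteria.

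The cost is one count query for each arm, two entries in Tab. 4 and a few sentences in 6.3.2. The register count can be obtained with the formal data request that section 7.1.4 already requires. No design change is needed.

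### The precision stated for a 5% WIdO subgroup (±1.20% to 1.38%) does not follow from its own inputs; the correct figure is about ±2.4 percentage points, 1.8 to 2 times as wide

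*Protocol*

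**What the plan says.** Protocol section 6.3.2 starts from a count for 2019, when "approximately 11,000 insured individuals aged 18-55 with a severe injury treated in an acute hospital were identified" in the nationwide WIdO data. Over a three-year inclusion period it expects that "around 33,000 severely and critically injured insured individuals will be included in the study". Tab. 4 in section 6.2 repeats the total: "33,000 severely and critically injured insured".

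The section then says that this size allows precise prevalence estimates even in small subgroups, and gives one worked example: "in a subgroup of 5% of the total number of patients, a prevalence of 50% could be estimated with a precision of" ±1.20% to 1.38%. The interval is specified as "two-sided exact binomial confidence interval 95% confidence interval". The choice of prevalence is explained: "A prevalence of 50% was chosen as it shows the greatest variation". The closing sentence adds that any other prevalence, or a larger subgroup, would be estimated more precisely.

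**The concern.** The example fixes everything that determines a binomial margin: total, subgroup share, prevalence, interval type, sidedness and level. The result can therefore be checked without assumptions, and ±1.20% to 1.38% looks far too narrow for about 1,650 patients.

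The form of the result is also odd. At a prevalence of exactly 50% the exact binomial interval is symmetric, so one subgroup size gives one margin and not a pair of different values.

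What is at stake is the only precision figure given for the WIdO arm. It is presented as the worst case for subgroups of 5% or more, and section 7.1.3 plans to describe unfavourable courses in trauma-specific subgroups and to analyse predictors within relevant subgroups. A reader who uses the sentence to judge how finely the cohort can be divided would expect margins little more than half their true size.

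**Working it through.** **Inputs, all from Protocol section 6.3.2**
- Total N = 11,000 per year × 3 years = 33,000 (same figure in Tab. 4)
- Subgroup share = 5%
- Prevalence p = 0.50
- Two-sided exact (Clopper-Pearson) interval, 95%

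**Step 1. Subgroup size.** n = 0.05 × 33,000 = 1,650, so x = 825 at 50%.

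**Step 2. Exact interval.** The lower limit is the 2.5% quantile of Beta(x, n − x + 1) = Beta(825, 826), which is 47.56%. The upper limit is the 97.5% quantile of Beta(x + 1, n − x) = Beta(826, 825), which is 52.44%. The margin is 2.44 points on each side.

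**Step 3. Cross-check by normal approximation.** 1.96 × √(0.25 / 1,650) = 1.96 × 1.231% = 2.41 points.

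**Step 4. Comparison with the stated figure.** 2.44 / 1.20 = 2.03 and 2.44 / 1.38 = 1.77.

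**Step 5. Size that the stated figure would need at p = 0.50.** By the normal approximation, n = (1.96 × 0.5 / margin)².

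| Margin | n, normal approximation | Share of 33,000 | n, exact interval | Share of 33,000 |
|---|---|---|---|---|
| 1.38 points | 5,043 | 15.3% | about 5,110 | 15.5% |
| 1.20 points | 6,669 | 20.2% | about 6,750 | 20.5% |

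With the share held at 5%, the total cohort would have to be about 101,000 to 133,000 (normal approximation: 5,043 / 0.05 and 6,669 / 0.05).

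**Step 6. Attempts to reproduce ±1.20% to 1.38% by another reading**

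| Reading | Result (points) |
|---|---|
| Standard error alone, n=1,650 | 1.23 |
| One-sided 95% bound, n=1,650 | 2.02 |
| Full width instead of half-width, n=1,650 | 4.88 |
| 5% of the register total in Tab. 4 (29,345, so n=1,467) | 2.59 |
| 5% of the combined total 33,000 + 29,345 = 62,345 (n=3,117) | 1.77 |

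None gives the stated pair. The standard error is close to 1.20, but it is not a 95% margin and does not produce 1.38.

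Unequal margins of this size do appear at low prevalence. With n=1,467 and p=6.4% the exact interval runs −1.20/+1.38, and with n=1,650 and p=7.5% it runs about −1.22/+1.38. A low-prevalence result may have been attached to the 50% statement. This is inference; the protocol does not say so.

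**Step 7. Is a looser convention used elsewhere?** No. Section 6.3.1 gives ±3% for n=1,000 and ±5.5% for n=300 at 50% prevalence. The normal approximation gives 1.96 × √(0.25 / 1,000) = 3.1 and 1.96 × √(0.25 / 300) = 5.7 points, so those figures agree with their inputs to rounding. The WIdO sentence is an isolated error.

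**The case against.** The strongest reply is that nothing depends on the figure. The WIdO cohort is not sized to a precision target. It consists of the insured people in existing 2015 to 2020 claims data who meet the criteria, and 33,000 is simply the expected yield. Correcting the sentence changes no sample size, endpoint, criterion or analysis. Nobody is recruited because of it, and the published intervals will be computed from the actual data. At ±2.4 points the general claim of useful precision in small subgroups is still reasonable: section 6.3.1 accepts ±5.5% for subgroups of 300 in the prospective cohort.

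All of this stands, and it limits the consequence. It does not make the figure right. The sentence makes a numerical claim, names its method, and presents the result as the least favourable case.

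It is also fair to say that the margin is twice as wide only against 1.20; against 1.38 the factor is about 1.8. Finally, since the source of the stated numbers is unknown, keeping them and changing the subgroup share to 15 to 20% would be a guess about which input was wrong, and would weaken a sentence meant to be about small subgroups.

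**Conclusion.** The stated precision is wrong. On the protocol's own inputs, a 5% subgroup of 33,000 gives ±2.44 percentage points at 50% prevalence with the exact interval the protocol names, against a stated ±1.20% to 1.38%. The understatement is a factor of 1.8 to 2.0, and the stated margin would need about three to four times as many patients in the subgroup (5,043 / 1,650 = 3.1; 6,669 / 1,650 = 4.0).

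The conclusion rests on no outside assumption, only on the total, share, prevalence and interval type printed in section 6.3.2. The sentence should be corrected because it is the only precision figure for this arm and claims a worst case that the true worst case exceeds. The cohort and the planned analyses are unaffected.

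**What to change.** In section 6.3.2, replace the example with a statement that in a subgroup of 5% of the cohort (n=1,650) a prevalence of 50% is estimated with a margin of ±2.4 percentage points (two-sided exact 95% binomial interval). The remarks that 50% is the least favourable prevalence and that larger subgroups do better can then stay.

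If the sponsor can trace ±1.20% to 1.38% to a different calculation, that figure could be kept, but only with the subgroup share or prevalence to which it applies. At 50% prevalence that means a subgroup of roughly 15 to 20% of the cohort. The first option is preferable because it follows directly from the stated inputs.

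Section 6.1.1 says that the criteria for identifying severe injury in the claims data are still to be revised, so the 33,000 is provisional. The margin should be recomputed once the cohort size is confirmed.

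The cost is one sentence and a less favourable number. Nothing in the conduct of the study changes.

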## **6.4 Recruitment Measures for the Prospective Cohort Study**

The recruitment of severely and critically injured patients will take place through clinics in the DGU Trauma Network during their stay in the study clinic. The study clinics will receive comprehensive training on the study procedure and the follow-up surveys (processes, content). The study clinics are certified DGU trauma centers and have extensive experience in treating severely injured patients, treating 50-250 patients per year according to the study's inclusion criteria (see above).

## **7. Methodology and Implementation**

To address the research questions, the project pursues a quantitative approach consisting of two cohorts of severely and critically injured patients, complemented by qualitative methods. Cohort 1 is a multicenter, non-interventional, prospective study focusing on clinical data, patient-reported experiences (PREs), and patient-reported outcomes (PROs). In Cohort 2, the focus is on retrospective analysis. For this, GKV routine data from the Scientific Institute of the AOK (WIdO) will be analyzed regarding patient pathways up to their reintegration into the workforce.

Qualitative methods are described in the ethical application 1 – qualitative study arm; these serve as the basis for parts of the questionnaire used in the multicenter, non-interventional, prospective cohort study. This questionnaire will be supplemented in the baseline survey by the DGU Trauma Register standard questionnaire (attached) and in the follow-up by existing instruments for surveying severely and critically injured patients identified through literature research.

